### Data analysis

Study data will be collected and managed using REDCap electronic data capture tools hosted at the University of Saskatchewan [22]. REDCap (Research Electronic Data Capture) is a secure, web-based application designed to support data capture for research studies, providing 1) an intuitive interface for validated data entry; 2) audit trails for tracking data manipulation and export procedures; 3) automated export procedures for seamless data downloads to common statistical packages; and 4) procedures for importing data from external sources.

#### Statistical analysis

All data will be descriptively analyzed using means, standard deviations, frequencies (where appropriate), and 95% confidence intervals. The sample size of 28 participants is sufficient for an initial phase 1 safety and tolerability study, but is too small for precise estimation of steady state levels of biologically active cannabinoids at each dose and for definitive assessments of efficacy. Trends will be examined and a medical statistician will assist with statistical and trend analysis of the data. Complete, specific details of the statistical analysis will be described and fully documented in the Statistical Analysis Plan (SAP) after completion of data collection.

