#### Secondary Objectives

To determine whether CBD-enriched *Cannabis* herbal extract will alter steady-state levels of co-administered anticonvulsant medications.To assess how treatment of pediatric patients with treatment refractory epileptic encephalopathy with CBD-enriched *Cannabis* herbal extract will affect the patient’s QoL.To determine the relation between dose escalation and steady-state trough levels of bioactive cannabinoids.To determine the relation between dose escalation and improvement in seizure frequency, QoL and incidence of adverse effects.

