##### *Study population*

The study will recruit participants between the ages of 1–10 years with an epileptic encephalopathy resistant to standard medical treatment. The study will aim to enroll 28 children from four Canadian cities (anticipated seven participants per site).

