**Fig. 1 Fig1:**
[figure not shown]
A flow chart of participant enrollment, treatment with CBD-Enriched *Cannabis* herbal extract, monitoring and weaning

Recruitment Phase: Prospective participants will be directly identified and recruited through the caregivers by study physicians at each study site. Any potential participants’ caregiver will be contacted by the study physician or pediatric neurology nurse either in-person at the study physician’s clinic or by telephone. Prospective caregivers of participants will be asked if they are interested in having their child participate in the study. If the response is positive, a copy of the study brochure and consent form will be provided to them. Caregivers of prospective participants will be asked to attend a recruitment visit after they agree to participate in the study and provide informed consent. During the recruitment visit, the participant will be screened for eligibility based on specific inclusion and exclusion criteria. If the participant qualifies for the study, the participants’ caregivers will be instructed on use the study diary.

Inclusion and exclusion criteria: Participation in this study is inherent on meeting the following inclusion criteria: (1) Participants must be between the ages of 1 and 10 years of age with treatment-resistant epileptic encephalopathy including: Infantile Spasms, Continuous Spike Wave in Sleep, Lennox Gastaut, Doose, Landau-Kleffner and Dravet Syndromes and Malignant Migrating Partial Seizures of Infancy. ‘*Treatment-resistant’* will be in keeping with the International League Against Epilepsy (ILAE) definition of failing two appropriate anticonvulsant medications at therapeutic doses. (2) Participants must experience a minimum of at least one major seizure *per* week or four major seizures *per* month. For the purposes of this study, major seizures will be motor seizures including: atonic, tonic, clonic, tonic-clonic, major myoclonic, myoclonic astatic seizures and epileptic spasms. (3) Participants must be available to attend study assessments regularly and enter data into the seizure monitoring logs correctly. (4) Negative pregnancy test at screening for females who have reached menarche.

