Weaning phase: Termination of treatment: At visit 6 (after completing 1 month of CBD at 10–12 mg/kg/day) participants will return to the clinic for a final series of tests which include: blood and urine analyses, quality of life and cognitive/developmental assessments, neurological and general pediatric assessments, and EEG. Participants will be provided with a one-month weaning schedule which incrementally decreases the dose of the 1:20 Δ^9^-THC:CBD *Cannabis* herbal extract administered (CBD at 8–9 mg/kg/day for 1 week then 5–6 mg/kg/day for 1 week then 2–3 mg/kg/day for 1 week prior to discontinuing the study product).

Final Assessment: Participants will return to the clinic upon completion of the one-month weaning period. Caregivers will provide observations of any side-effects noted during the weaning period and will complete a final quality of life questionnaire. Data from the seizure monitoring diaries will be collected and caregivers will be asked to return any leftover study drug.

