### Sample size determination

As CARE-E is a phase I dose escalation safety and tolerability study designed to find the most appropriate dose of CBD in a pediatric population it was felt that power analysis was not required to calculate sample size. The sample size of 28 participants each receiving 4 separate dosage escalations is within usual guidelines for standard phase I clinical trial designs. In this multi-site dose escalation study, we chose to escalate within the same participant with 7 participants at each site because the low pediatric population incidence of epileptic encephalopathy (the inclusion criterion), precluded ability to escalate in cohorts of 6, where a new cohort of six would be administered the next dosing level [20, 21]. Any patient exhibiting a dose limiting toxicity will not receive the next dose escalation.

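### Means and SDs for all data suit seizure counts poorly, and a trend over the fixed upward escalation cannot separate dose from time on study

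*Protocol article*

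**What the plan says.** The Statistical analysis section of the protocol article fixes one form of summary for everything: "All data will be descriptively analyzed using means, standard deviations, frequencies (where appropriate), and 95% confidence intervals". It adds: "Trends will be examined and a medical statistician will assist with statistical and trend analysis of the data". Details are left to a SAP to be written once data collection is complete. The section also says that 28 children are too few for definitive efficacy conclusions.

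Seizure frequency and duration form the second primary objective, worded as monitoring. A secondary objective is "To determine the relation between dose escalation and improvement in seizure frequency, QoL and incidence of adverse effects". Sample size determination calls the trial "designed to find the most appropriate dose of CBD in a pediatric population" and says "it was felt that power analysis was not required to calculate sample size".

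On the data: "The study will aim to enroll 28 children from four Canadian cities (anticipated seven participants per site"). The inclusion criteria set only a floor on counts ("Participants must experience a minimum of at least one major seizure" per week, or four per month). All children escalate at fixed monthly intervals, and there is no control arm. Daily seizure diaries run through a one-month untreated baseline, the four treatment months and the weaning month. For the final visit the article says "Data from the seizure monitoring diaries will be collected". It gives no particular analytic use to the baseline or weaning diaries.

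**The concern.** There are two separate problems with the stated method, and a smaller third.

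**Scale.** Counts with a floor and no ceiling, across syndromes from infantile spasms to Dravet, are likely to have a long right tail. The mean and SD of such counts in 28 children describe a handful of children, and a t-interval around the mean is unreliable. The typical child's change could be hidden or even reversed in sign. Plasma levels raise the same issue.

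**Dose and time.** Every child meets the doses in the same order, one per month. Anything that drifts over four open-label months (natural fluctuation, expectation, tolerance) moves in step with dose. A trend over the escalation therefore carries both, while the objectives ask about dose.

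**Who is at each dose.** Children with dose-limiting toxicity do not receive the next escalation. Tolerability at the upper levels, if given only among those who reached them, would look better than it is in all treated children.

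**Working it through.** **The plan's own figures.** 4 sites × 7 children = 28, as stated. No power, alpha, effect size or SD is given, so there is no sample-size calculation to reproduce. The dosing example agrees with itself: 25 kg × 2.5 = 62.5, rounded to 60 mg, and 60/25 = 2.4 mg/kg/day.

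**Dose against month (documents' figures only).** The mid-points of the four treatment ranges are 2.5, 5.5, 9 and 11 mg/kg/day for months 1 to 4; the article says the mid-point is prescribed. The mean dose is 7.0 and the mean month 2.5. The sum of cross-products is 14.5; the sums of squares are 42.5 for dose and 5.0 for month.

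- r = 14.5 / √(42.5 × 5.0) = 14.5 / 14.577 = 0.995
- Variance inflation = 1 / (1 − 0.9894) = 94

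Suppose there is no dose effect, but counts fall by a fraction q each month. The change at month k is (1 − q)^k − 1:

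| q (assumed) | Month 1 | Month 2 | Month 3 | Month 4 |
|---|---|---|---|---|
| 5% | −5% | −10% | −14% | −19% |
| 10% | −10% | −19% | −27% | −34% |
| 15% | −15% | −28% | −39% | −48% |

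Each row would look like a graded response to dose.

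**Skew (assumed distributions).** 28 children, log-normal counts, 20,000 simulated trials:

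| SD of log count | Share of seizures in top two children | Coverage of 95% t-interval for mean |
|---|---|---|
| 1.0 | 29% | 88% |
| 1.5 | 43% | 78% |
| 2.0 | 56% | 65% |

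A constructed example shows the sign problem. Let 25 children go from 20 to 10 seizures a month and three from 600 to 720. The group mean goes from 2300/28 = 82.1 to 2410/28 = 86.1, a rise of 4.8%. The median child falls by 50%. The geometric mean ratio is (0.5^25 × 1.2^3)^(1/28) = 0.55, a fall of 45%.

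**Can the weaning diary separate dose from time?** On weekly data, with 4 baseline weeks at dose 0 and 16 treatment weeks, r = 0.978 and the variance inflation is 23. Adding weaning weeks at 8.5, 5.5, 2.5 and 0 mg/kg/day brings r to 0.58 and the inflation to 1.5 (0.76 and 2.3 with only the three dosed weeks). So collinearity drops sharply. Bias is another matter. I fitted weekly log count on dose plus linear week over all 24 weeks, with a true dose effect of zero and no noise:

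| Assumed pattern | Spurious effect at 11 mg/kg/day |
|---|---|
| 30% fall in the 16 treatment weeks, gone at weaning | −34% |
| 30% fall from treatment start that persists | −12% |
| 30% rise in the weaning weeks only | −19% |

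The first is as large as the artefact from a 10% monthly drift.

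**The case against.** **Deferral to the SAP.** The strongest reply is that this is an article's short summary and that outcome scale and model belong in the SAP. That stands as far as missing detail goes: the absence of a repeated-measures model is no fault here. It does not dispose of the point, because the section does state a summary for all data, and that choice suits counts badly.

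**Raw counts.** A reader might infer that means of raw counts are planned. The article does not say so; a mean within-child percent change or log ratio would also fit the wording. The skew argument applies to means of counts.

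**Trend read as dose effect.** A reader might also infer that the plan will report a trend as a dose-response and carry it into Phase II. Nothing in the document says that. It speaks only of examining trends, and the Discussion calls the study primarily one of safety. What remains is that the objective asks about dose and the Statistical analysis section does not say that the trend mixes dose with time. Its small-sample caveat concerns precision, and more children would not remove the confounding.

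**Diaries as a cure.** It is tempting to say that the weaning diaries resolve the confounding. They do not, as the last table shows: lower collinearity helps only if the assumed form of the time effect is right.

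**Assumed variances.** No seizure variance is given, and counting a cluster as one seizure may limit extreme values. The sizes are therefore illustrative. The gain from a log ratio also varies. With an SD of log ratio of 0.6, its interval excludes zero in about 86% of simulated trials, against 31% to 13% for the mean change (SD of log count 1.0 to 2.0). Adding month-to-month variation, with a between-child SD of 0.5 for the log effect, gives 50% to 47% against 21% to 8%. The direction is the same in both.

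**Selection.** Data from withdrawn children are retained, and children with significant side-effects move to a mid-point dose. This softens the third problem but does not settle the denominator.

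**Conclusion.** The point holds in limited form. Dose and treatment month are nearly the same variable under the protocol's own schedule (r = 0.995), so an ascending trend cannot be assigned to dose; this needs no outside assumption. Mean-and-SD summaries of seizure counts would probably be dominated by a few children. The size of that (top two children with 29% to 56% of seizures, interval coverage of 88% down to 65%) depends on assumed SDs of log count from 1.0 to 2.0. Both affect the exploratory seizure and dose reading. They do not undermine a definitive efficacy claim, because the article makes none, and the safety objective is touched only through the denominator used at each dose. It should be put right, but it does not invalidate the trial.

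**What to change.** Before the data are examined:

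- **Seizure summary.** Name the within-child ratio to the baseline month as the main summary (geometric mean ratio with 95% CI, stating how zero counts are handled), with the median and quartiles beside it. Use geometric means or medians for plasma levels.
- **Trend wording.** State that any trend over the ascending doses is dose and time combined and does not by itself support a dose-response conclusion.
- **Tolerability.** At each dose level, report it out of all treated children, alongside the number who reached that level.
- **Optional sensitivity analysis only.** Model weekly diary counts from baseline, treatment and weaning on dose taken and study week, with and without the weaning weeks. State that it assumes a form for time and does not remove expectation, carry-over or withdrawal effects.

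The cost is some wording and a little more analysis. No new data are needed, since the diaries are already collected.

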## Abstract

**Background:**

Initial studies suggest pharmaceutical grade cannabidiol (CBD) can reduce the frequency of convulsive seizures and lead to improvements in quality of life in children affected by epileptic encephalopathies. With limited access to pharmaceutical CBD, *Cannabis* extracts in oil are becoming increasingly available. Physicians show reluctance to recommend *Cannabis* extracts given the lack of high quality safety data especially regarding the potential for harm caused by other cannabinoids, such as Δ^9^-tetrahydrocannabinol (Δ^9^-THC). The primary aims of the study presented in this protocol are (i) To determine whether CBD enriched *Cannabis* extract is safe and well-tolerated for pediatric patients with refractory epilepsy, (ii) To monitor the effects of CBD-enriched *Cannabis* extract on the frequency and duration of seizure types and on quality of life.

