**Methods:**

Twenty-eight children with treatment resistant epileptic encephalopathy ranging in age from 1 to 10 years will be recruited in four Canadian cities into an open-label, dose-escalation phase 1 trial. The primary objectives for the study are (i) To determine if the CBD-enriched *Cannabis* herbal extract is safe and well-tolerated for pediatric patients with treatment resistant epileptic encephalopathy and (ii) To determine the effect of CBD-enriched *Cannabis* herbal extract on the frequency and duration of seizures. Secondary objectives include (i) To determine if CBD-enriched *Cannabis* herbal extracts alter steady-state levels of co-administered anticonvulsant medications. (ii) To assess the relation between dose escalation and quality of life measures, (iii) To determine the relation between dose escalation and steady state trough levels of bioactive cannabinoids. (iv) To determine the relation between dose escalation and incidence of adverse effects.

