##### *Study design*

The CARE-E trial is a phase 1, open-label, dose-escalation study consisting of 4 separate phases: recruitment, baseline, treatment, and weaning. The recruitment phase involves the selection of eligible participants using pre-established exclusion and inclusion criteria (described below). The baseline phase establishes baseline values for each experimental measurement prior to treatment with the study product. During the treatment phase, caregivers of participants administer dosages of the CBD-enriched *Cannabis* herbal extract twice daily to their children escalating at fixed one-month intervals over the course of four-months. Upon completion of the treatment phase, participants will enter the weaning phase and caregivers will slowly taper the participants off of the CBD-enriched *Cannabis* herbal extract using a one-month weaning schedule.

During the study, caregivers will monitor the participants for any potential side effects and will use a study diary to record their child’s seizure activity by tracking seizure frequency and duration, and any use of rescue medications to abort prolonged seizures. The participant’s condition as well as drug levels and biomarkers of toxicity will be monitored on a monthly basis. Testing will include blood and urine analysis, QoL assessments, neurological and general pediatric assessments, and an electroencephalogram (EEG) recorded for 2 h or until sleep is obtained (Fig. 1).

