Monthly follow-up: Caregivers will return to the clinic for the monthly testing as described above. Data from the study diaries will be copied for analysis. Following the completion of testing, parents will receive a new 33-day supply of the 1:20 THC:CBD *Cannabis* herbal extract from the research pharmacist. Parents will be instructed to administer the extract at increasing doses over the next 3 months; i.e. at 5–6 mg/kg/day divided BID at visit 3, 8–10 mg/kg/day divided BID at visit 4, and 10–12 mg/kg/day divided BID at visit 5. If the participant experiences significant side-effects at a certain dose, the subsequent CBD dose will be adjusted to the mid-point between their current dose and former dose. Parents will be instructed to continue tracking their child’s seizure activity and monitoring the child for potential side effects in the same manner as the initiation of therapy month.

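### The SAP is scheduled for after data collection in an open-label trial, so open analysis choices can be made knowing participants' outcomes; separately, the abstract lists quality of life as a primary aim and the objectives do not

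*Protocol article*

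**What the plan says.** **Timing of the SAP.** The Statistical analysis section commits to descriptive summaries of all data with 95% confidence intervals and says that trends will be looked at with a statistician's help. Everything more specific is to be "fully documented in the Statistical Analysis Plan (SAP) after completion of data collection". The same section says that the sample "is too small for precise estimation of steady state levels of biologically active cannabinoids at each dose and for definitive assessments of efficacy".

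**Blinding and access to data.** Under Study design: "The CARE-E trial is a phase 1, open-label, dose-escalation study". No control group is described. The same section says that "drug levels and biomarkers of toxicity will be monitored on a monthly basis", and it includes quality-of-life assessment in the testing. The monthly follow-up paragraph adds: "Data from the study diaries will be copied for analysis".

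**Objectives.** The abstract's Background gives primary aim (ii) as the effects of the extract "on the frequency and duration of seizure types and on quality of life". The abstract's Methods gives primary objective (ii) as the effect of the "herbal extract on the frequency and duration of seizures", without quality of life, and lists as a secondary objective "To assess the relation between dose escalation and quality of life measures". The Methods/Design section agrees with the abstract's Methods on the tier: quality of life is absent from the primary objectives and appears under Secondary Objectives.

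**The concern.** A protocol may leave analysis detail to a SAP, and that is no fault. Here, however, the protocol itself states when the detail will be decided, and the time it names is too late for an unblinded trial. A SAP written after the last visit can still be sound if treatment allocation is masked, because its authors cannot tell which choice favours the product. In this trial nothing is masked. By the end of data collection the site teams will have followed each child from baseline through four dose steps, and they know what every child received.

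Without a control arm or blinding, prior specification is one of the few safeguards left against choosing the summary that looks best. That matters because the Discussion presents the study as groundwork for a larger phase II efficacy trial and as a source of confidence for prescribers. A baseline contrast, seizure grouping or trend model chosen with the outcomes in mind would carry its optimism into that next trial.

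The two placements of quality of life are a separate and smaller fault. As the text stands, a report could call quality of life primary or secondary and cite the protocol for either.

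**Working it through.** No arithmetic measures the effect of SAP timing. The only related figure, the sample size, is consistent: 4 sites × 7 participants = 28. The check is a comparison of the text.

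**Step 1. Who knows what before the SAP exists**

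| Item | Where stated | Known to sites during the trial? |
|---|---|---|
| Treatment and dose received | Study design (open-label) | Yes, always |
| Seizure diaries | Monthly follow-up | Yes, copied at each visit |
| Laboratory safety tests | Complete blood counts and clinical chemistry | Yes, run at local hospital laboratories at each visit |
| Quality of life | Study design | Yes, assessed monthly |
| Cannabinoid levels | Study design; Bioactive cannabinoid plasma concentrations | Monthly monitoring is stated, but samples are frozen until assay, so possibly later |

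This is knowledge of individual participants. The article describes no pooled review of outcomes while the trial runs.

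**Step 2. What is already fixed**

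- Seizure monitoring: the same three seizure types are tracked throughout, and a cluster counts as one seizure.
- Complete blood counts and clinical chemistry: the laboratory panel is listed, and a result outside the local age-specific reference interval counts as an adverse event.
- Quality of life assessment: item recoding, subscale means and the total score are set, and the 13 added items have their own total.
- Statistical analysis: descriptive statistics with 95% confidence intervals for all data.

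**Step 3. What remains open until the SAP**

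1. Trend analyses: no outcome, model or contrast is named.
2. Contrasts from baseline: none is defined for seizures or quality of life.
3. Seizure groupings: it is not said whether the tracked types are reported singly, together, or restricted to the major motor types used for eligibility.
4. Denominators: withdrawn participants are not replaced and their data are kept, but who counts at each dose step is not stated.
5. Adjusted or halted dose steps: Monthly follow-up provides for a mid-point dose after significant side effects, and Sample size determination says that a child with a dose-limiting toxicity is not escalated. To which step such data belong is not stated.

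Each of these would ordinarily be left to a SAP, and none is a fault by itself. The fault is that the stated timing lets all five be settled after Step 1 has run its course.

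**Step 4. The objective lists**

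| List | Safety and tolerability | Seizure frequency and duration | Quality of life |
|---|---|---|---|
| Abstract, Background | Primary | Primary | Primary |
| Abstract, Methods | Primary | Primary | Secondary |
| Methods/Design, Objectives | Primary | Primary | Secondary |

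Safety and seizures agree in all three lists. Quality of life is primary in one and secondary in two. The abstract's secondary objective concerns its relation to dose, which alone could sit beside a primary aim on its overall level. Methods/Design, however, lists the effect of treatment on quality of life as secondary, so the same question does stand in two tiers.

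**The case against.** The strongest reply is that this is a descriptive phase 1 study with no hypothesis test, no stated alpha and an explicit statement that it is too small for definitive conclusions on efficacy, so no error rate can be breached. That stands, and it lowers the severity. It does not remove the point, because the plan still includes confidence intervals and trend analysis, and the results are meant to shape a later efficacy trial.

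A second reply is that completing data collection is not the same as analysing the data, so the SAP could still precede any pooled result. That is a fair reading. With no masking, though, the interval between the last visit and the first pooled table gives little protection, since those who shape the SAP may already know how individual children did.

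A third reply is that much is already fixed, as Step 2 shows. This also stands: the latitude is limited to the five items in Step 3. The cited trial registration may define the outcomes further, but its content is not in the article.

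Three stronger conclusions might be inferred, and the document supports none of them:

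- *That outcomes and analyses can be freely chosen once all results are known.* Individual monitoring at four sites is not a pooled result, and the outcome measures and their scoring are largely set.
- *That the harm can be expressed as the chance that at least one of many 95% intervals excludes no change.* That calculation measures multiplicity. A SAP signed before the first participant and listing the same intervals would give the same figure. It also needs a grid of contrasts that the protocol does not define, and an independence that repeated measures on the same 28 children cannot have.
- *That safety should become the only primary objective.* The Discussion does stress safety, but all three lists name seizure frequency and duration as primary. Moving them would change an objective, not correct an inconsistency.

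**Conclusion.** The point holds within limits, at the level of should-fix. The protocol states a time for the SAP that, in an open-label study with no control group described, lets five kinds of open analysis choice be made with knowledge of participants' outcomes. Protection against selective analysis is weakened; the document does not show that selection will occur, and it gives no basis for a numerical estimate of its effect.

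The inconsistency in objectives is confined to quality of life and to one phrase in the abstract's Background.

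The conclusion assumes that those who write or advise on the SAP include, or are in contact with, people who have seen site data, and that no earlier dated document already settles the open choices. The article states nothing to the contrary on either.

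**What to change.** 1. In the Statistical analysis section, replace the timing sentence with wording such as: *The SAP will be finalised, signed and dated before any treatment-phase outcome data are summarised or exported for analysis. Any analysis defined after that date will be reported as post hoc.* Monthly safety review of individual participants is unaffected.
2. In the abstract's Background, remove quality of life from primary aim (ii), so that it is secondary as in the abstract's Methods and in Methods/Design.
3. Leave seizure frequency and duration in the primary tier, where all three lists place them.

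The cost is two changes of wording and bringing forward a document that has to be written anyway. No further participants, visits or data are needed.
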